### Message Tailoring

Tailoring involves creating communications in which information about an individual is used to determine specific content he or she receives [15,54]. Positive effects of tailoring have been demonstrated in changing diet and PA behaviors [15-17,55]. The intention of tailoring, which uses characteristics unique to the individual, is to improve behavioral outcomes by altering processing or making the message more acceptable [54,56]. These characteristics can include personal behaviors, psychosocial characteristics, and dietary and PA behaviors. Specific strategies for message tailoring include personalization, feedback, and content matching [54]. This study will focus on personalized feedback (exemplified in Table 3) using information obtained on diet and PA behaviors at baseline and specific time points throughout the intervention. Digital elements (food and beverage images and graphical presentation of PA data) will be included to enable evaluation of these components.

### Tailored Dietary Feedback

Tailored dietary feedback will be formulated by the research dietitian based on food group analysis of the 4-day mFR. Feedback will focus on key messages encouraging daily energy reduction of 2000 kJ by avoiding or limiting EDNP foods, sugar-sweetened beverages, and alcohol; eating less at meals or additional snacks (except for salad and vegetables); and eating less often. Food group serves will be categorized for each participant based on three defined target zones (not achieved, almost achieved, and achieved). A template will be used for each dietary feedback email, modified according to the results of each participants’ dietary analysis. For EDNP serves, the template will be modified according to dietary intake to indicate average daily serves of “junk” foods, sugary drinks, and alcohol and kilojoule intake. Participants will be shown an image of their dietary sources of EDNP food and beverages. For fruit and vegetable serves, a scripted message will be devised for three levels of intake: (1) low: 0 to <3.5 serves of fruits and vegetables, (2) medium: 3.5 to <7 serves of fruits and vegetables, and (3) meeting the recommendation: at least 2 serves of fruits and 5 serves of vegetables per day. Individual mFR images will be incorporated into email templates to illustrate the sources of EDNP foods, fruits, and vegetable serves. Two to three suggested modifications will be provided to each participant to support them in achieving the daily energy-reduction goal.

### Tailored Activity Feedback

Individual activity data will inform PA feedback based on activity monitor recordings 1 week prior to the feedback time point. The data will be automatically imported into a research platform (Fitabase) to facilitate monitoring and analysis of continuous back-end data. Messages will focus on the three movement goals: “move more” (step count; toward ≥10,000 steps), “move harder” (minutes spent in MVPA; towards ≥30 active minutes), and “move more often” (hourly movement; towards ≥250 steps per hour). Participants will receive tailored email feedback regarding their current activity, and guidance on goal progression to classify goal achievement (not achieved, almost achieved, or achieved).

### Control Groups

The online control group will complete online self-report questionnaires only, while the active control group will also undertake face-to-face data collection and record dietary intake (mFR app) and PA behaviors (accelerometery) at baseline, 6 months, and 12 months. Neither group will receive tailored messaging or feedback on their dietary intake or PA. As an incentive for retention, active control participants will be advised that they will receive feedback upon study completion, and the online control group will be entered into a 6-monthly prize draw to encourage ongoing participation.

### Economic Evaluation

An economic evaluation will be conducted to consider the relative costs and outcomes of the intervention. To facilitate a cost-utility analysis, the EuroQol-5D will be administered. This is a widely used instrument specifically designed to capture quality of life for health economics [57]. This study will use the five-level version of the instrument to identify sensitive and small, but important, changes in health-related quality of life [58]. Quality-adjusted life years will be estimated for intervention and control groups. Concerning costs, we will collect the time needed to provide tailored advice to participants, medication and supplement use (name, dose, and frequency), and family expenditure on groceries. This will allow economic evaluation from the perspective of the health system (by considering only the cost of the intervention and medication) and a broader society (by considering all costs). Univariate and multivariate sensitivity analyses will be undertaken. In particular, the impact of different methods of extrapolating costs and outcomes beyond the horizon of the trial will be assessed. The costing model will include resources required to assess ongoing maintenance of the mFR and wearable activity monitors, including changes as a result of upgrades to operating systems. We will also record minor costs of ongoing use (SMS messages and email communication). The major cost of the intervention is likely to be provision of tailored advice based on data received (research personnel and research platform costs). This will be estimated by recording time spent deconstructing the mobile app data, the Web app, and objective measures and then interpreting data and constructing appropriate feedback.

**Table 3 table3:** Examples of tailored feedback intervention strategies.

Type^a^	Example	Processing and goals
Descriptive (what is known)	Hi Jane, it’s the team with your feedback. So how did you score? Ave fruit serves = 1.5, ave veg serves = 3. What’s the goal again? 2 fruit & 5 veg every day. You are halfway there!	Effortful processing and self-referencing
Comparative (contrasts with others)	Hi Jane, so how did you score? Ave fruit serves = 1.5, veg serves = 3.5. Your fruit serves varied from 0 - 3.5, veg from 1.5 - 5.5 over 4 days. So how does your intake compared to others? Ave fruit serves = 1, veg serves = 2.	Effortful processing, self-referencing, and normative beliefs and attitudes
Evaluative (interpretation)	Hi Jane, it’s the team with feedback on your PA. So how did you score? Ave steps a day = 5,500. What’s your goal again? 10,000 steps a day. You are over halfway there!	Effortful processing, self-referencing, and normative beliefs and attitudes

^a^Adapted from [54].

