**Methods:**

All eligible participants will provide data on demographics and lifestyle behaviors online at baseline, 6 months, and 12 months. Using two-stage randomization, participants will be allocated into one of three conditions (n=200 per group): tailored feedback delivered via email at seven time points, informed by objective dietary (mobile food record app) and activity (wearable activity monitor) assessment; active control receiving no tailored feedback, but undergoing the same objective assessments as tailored feedback; and online control receiving no tailored feedback or objective assessments. Primary outcome measures at 6 and 12 months are changes in body mass, EDNP food and beverage consumption, and daily moderate-to-vigorous PA (measured via accelerometry). Secondary outcomes include change in fruit and vegetable consumption, daily sedentary behaviors, and cost effectiveness.

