### Physical Activity Assessment

Physical activity and sedentary behavior will be assessed with a hip-worn Actigraph GT3X+ accelerometer to quantify change in average MVPA and sedentary time for the face-to-face (active control and tailored feedback) groups. The accelerometer will also enable the assessment of sleep. The participants will be instructed to wear the accelerometer on their right hip 24/7 for 7 consecutive days. Commonly used cut-off points will be used to classify each minute of accelerometer data as sedentary (<100 counts per minute) [46], light intensity (100-1951 counts per minute), moderate intensity (1952-5724 counts per minute), or vigorous intensity (>5724 counts per minute) [47].

A wrist-worn activity monitor (Fitbit Charge 2) will be provided to the tailored feedback group to enable 24/7 continuous self- and researcher monitoring of step count, MVPA, and hourly movement to inform PA feedback. Participants will be asked to wear the monitor at night to enable the assessment of sleep. With informed consent, activity monitor data will be automatically imported into a back-end research platform (Fitabase) to facilitate PA behavior data monitoring, extraction, and analysis by researchers.

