### Statistical Analysis

The following primary outcome variables will be measured at baseline and 12 months of the intervention: changes in body mass, EDNP food and beverage consumption (sugar-sweetened beverages, alcohol, and take away and other “junk” foods), and daily minutes spent in MVPA. Secondary outcome variables include changes in fruit and vegetable serves and daily minutes spent in sedentary activity. Outcomes will identify characteristics of responders who remained engaged and reported improvements in key behaviors and quantify resource use associated with each arm of the study, which will be used in an economic evaluation of tailored feedback. Data on change in outcome variables in each of the two groups will be compared using analysis of covariance. Assumptions of the analyses will be assessed by examining residuals. Data will be transformed if assumptions of the analyses are not satisfied. Possible covariates considered will include age, sex, country of birth, ethnicity, highest education level, socioeconomic index for area, and baseline value of the variable analyzed. *P*-values < .05 will be considered statistically significant. Effect size of differences between treatment and control will be expressed as adjusted mean difference and associated 95% CIs. Data on change in outcome variables postintervention and follow-up time points will be converted into binary categorical variables and analyzed using multivariable logistic regression and generalized estimating equations. Odds ratio and associated 95% CIs will be reported. The analyses will identify characteristics of participants who are least likely to change their consumption of EDNP foods, PA, and BMI, thereby identifying target groups for future health promotion interventions.

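### The societal cost analysis claims to consider all costs but records household spending as groceries only, although the intervention targets take-away food and alcohol

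*Protocol article*

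**What the plan says.** Cost effectiveness is a secondary outcome. The Abstract (Methods) states: "Secondary outcomes include change in fruit and vegetable consumption, daily sedentary behaviors, and cost effectiveness".

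The Economic Evaluation section names the cost data to be collected: the time taken to give tailored advice, then "medication and supplement use (name, dose, and frequency), and family expenditure on groceries". It says that this collection will permit two perspectives. One is the health system, "by considering only the cost of the intervention and medication". The other is "a broader society (by considering all costs").

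The Statistical Analysis section spells out the primary outcome of energy-dense nutrient-poor (EDNP) food and beverage consumption as "sugar-sweetened beverages, alcohol, and take away and other" junk foods. The Tailored Dietary Feedback section directs the messages at EDNP foods, sugary drinks and alcohol, and also at smaller and less frequent eating. Table 2 adds goals to raise fruit and vegetable intake.

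**The concern.** A societal cost analysis of a diet intervention should record the household spending that the intervention is meant to change. Here the only household spending item is groceries. Take-away meals, eating out and alcohol bought at a bar or restaurant do not fall naturally under that word, and no other listed cost item covers them.

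The difficulty is one of asymmetry. If a tailored-feedback participant gives up take-away food and cooks at home instead, the added spending lands inside the measured item and the saved spending lands outside it. Randomisation does not remove this, because the shift in spending is itself part of the treatment effect. A later analysis plan cannot properly repair it either, because it cannot analyse spending that was never asked about.

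At stake is the numerator of the societal cost-utility result, one of the two perspectives on which the protocol's interest in scaling up would draw.

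**Working it through.** The documents give no price, cost or cost-effectiveness ratio, so there is no stated figure to reproduce. The check compares what is collected with what is targeted, and then asks what the gap does to the incremental cost.

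**Step 1. Collected against targeted.**

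| EDNP component (Statistical Analysis) | Covered by a listed cost item? |
|---|---|
| Sugary drinks | If bought with groceries, yes; otherwise no |
| Alcohol | Depends on the question wording, which is not shown; bought out, no |
| Take-away | No |
| Other junk foods | If bought with groceries, yes; otherwise no |

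Fruit and vegetables, which the feedback tries to increase, would mostly be groceries and so would be counted.

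**Step 2. The error in the incremental cost.** Let dG be the between-group difference in grocery spending and dO the difference in all other food and drink spending.

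- Food component of a full societal cost: dG + dO
- Food component as recorded: dG
- Error (recorded minus full): dG − (dG + dO) = −dO

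If the intervention lowers outside spending by S, then dO = −S and the societal incremental cost is overstated by S. If the EDNP reduction comes wholly from supermarket items, dO = 0 and there is no error. If participants eat out more expensively, dO is positive and the cost is understated. The documents give no information on dO, so neither size nor sign can be derived from them.

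**Step 3. Illustration of scale.** The only documentary inputs are the 0.6 serves/day difference in the Power section and the 600 kJ serve in the Dietary Assessment section. They agree with each other: 0.6 × 600 = 360 kJ/day, as the Power section states. Treating 0.6 as a mean reduction sustained for a year is an assumption:

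- 0.6 × 365 = 219 serves per year

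Assume 0.50 to 3.00 dollars per serve, with 20% to 60% of the displaced serves bought outside groceries:

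- Low: 219 × 0.50 × 0.20 = 21.9 dollars
- High: 219 × 3.00 × 0.60 = 394.2 dollars

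Under these assumptions about 22 to 394 dollars per participant-year of saving would go unrecorded. The range is wide because both the price and the share are assumed. It shows that the omission need not be trivial; it is not an estimate for this trial.

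**The case against.** The strongest reply is that the second perspective is set against one that counts only intervention and medication, so it can be read simply as all the costs just listed. On that reading the fault is one of labelling. This is fair, and it is why narrowing the label is an acceptable remedy. It does not make groceries an adequate measure for a societal analysis of an intervention aimed at take-away food and alcohol.

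A second reply is that success need not raise grocery bills. The messages also ask people to eat less and less often, and sugary drinks and junk foods are often bought with groceries. The question wording is not shown and may capture some alcohol. This stands, and it is why no direction is claimed here. A reader might infer that the societal result is biased against the intervention; the documents do not support that.

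A third reply is that the food record and the online food questionnaire measure intake, which could be priced. No such costing is stated, and intake data describe the participant, not what the family spent.

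Three stronger readings are tempting but not supported:

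- **The activity monitor's price is left out.** "A wrist-worn activity monitor (Fitbit Charge 2) will be provided to the tailored feedback group", and its purchase is not named among the costs. But the cost of the intervention is a general heading, the model description is not exhaustive ("The costing model will include resources required to assess ongoing maintenance of the mFR and wearable activity monitors"), and the price can be taken from the trial's own accounts.
- **Family spending is mismatched with participant-level quality-adjusted life years.** Household spending is a legitimate societal cost.
- **Health-service use is missing.** A condensed article may leave such detail to the full protocol or economic plan.

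**Conclusion.** The point holds in a limited form. As described, the listed cost items do not support a societal perspective that considers all costs, because spending on take-away, eating out and alcohol bought outside groceries is not among them, while alcohol and take-away belong to the primary diet outcome.

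The consequence is confined to the societal perspective of a secondary outcome. Food spending does not enter the health-system perspective at all, so it would be wrong to say that the whole economic conclusion depends on this item. The article also expects the main intervention cost to lie elsewhere: "The major cost of the intervention is likely to be provision of tailored advice based on data received (research personnel and research platform costs"). The planned sensitivity analyses could vary assumptions about outside spending but could not supply the missing data.

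The size and net direction of the error cannot be determined. The 22 to 394 dollar illustration rests on assumed prices, an assumed share bought outside groceries, and the 0.6 serves/day difference being achieved and sustained. A reader might wish to turn it into a shift in cost per quality-adjusted life year. The documents give no expected gain in quality of life, so any such figure would be driven by an invented denominator.

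This is a worthwhile and inexpensive improvement, not a flaw that threatens the trial's primary results.

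**What to change.** In the Economic Evaluation section, and in the questionnaire behind it, replace the grocery item with household spending on all food and drink, including take-away, eating out and alcohol. Ask it at baseline, 6 months and 12 months. Keep groceries as a separate line within it, so that answers already given remain comparable.

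Where earlier participants answered only the grocery item, or if the item is not widened, describe the second perspective as intervention, medication and grocery costs instead of all costs. Report it under that name and state that outside food and alcohol spending was not measured.

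Cost: one reworded question with a few sub-items, and a slightly longer questionnaire. Enrolment began in August 2017, so participants already enrolled would have no matching baseline for the wider item. Relabelling is a wording change and remains possible at any stage.

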### Process Evaluation

Process evaluation will assess to what extent the intervention reached the target audiences. A brief questionnaire will be used to evaluate participants’ perception of the tailored feedback (ie, message persuasiveness, message tone, readability, ease of understanding, usefulness of advice, suitability, and relevance to age group) and to comment on features they like/dislike about the program. Usability feedback will also be obtained for the mFR (tailored feedback and active control groups) and activity monitor (tailored feedback group only). Impact evaluation will consist of exit interview surveys via telephone at 14 months to assess intervention impact as well as perceptions of various strategies and materials. Selected program completers and noncompleters (tailored feedback and active control groups) will be invited to participate in one-on-one interviews concerning their perceptions of the ToDAy intervention.

### Statistical Analysis

The following primary outcome variables will be measured at baseline and 12 months of the intervention: changes in body mass, EDNP food and beverage consumption (sugar-sweetened beverages, alcohol, and take away and other “junk” foods), and daily minutes spent in MVPA. Secondary outcome variables include changes in fruit and vegetable serves and daily minutes spent in sedentary activity. Outcomes will identify characteristics of responders who remained engaged and reported improvements in key behaviors and quantify resource use associated with each arm of the study, which will be used in an economic evaluation of tailored feedback. Data on change in outcome variables in each of the two groups will be compared using analysis of covariance. Assumptions of the analyses will be assessed by examining residuals. Data will be transformed if assumptions of the analyses are not satisfied. Possible covariates considered will include age, sex, country of birth, ethnicity, highest education level, socioeconomic index for area, and baseline value of the variable analyzed. *P*-values < .05 will be considered statistically significant. Effect size of differences between treatment and control will be expressed as adjusted mean difference and associated 95% CIs. Data on change in outcome variables postintervention and follow-up time points will be converted into binary categorical variables and analyzed using multivariable logistic regression and generalized estimating equations. Odds ratio and associated 95% CIs will be reported. The analyses will identify characteristics of participants who are least likely to change their consumption of EDNP foods, PA, and BMI, thereby identifying target groups for future health promotion interventions.

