### Power

A sample size of 600 participants (n=200 per group) will have sufficient power to detect a change in the primary outcome variable of at least 0.6 median serves/day of EDNP (discretionary) foods (or equivalent to a 360 kJ/day reduction) between groups at 90% power and 5% level of significance. Assuming a drop-out rate of 20%, a total of 600 participants will be recruited.

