## Results

Enrollment commenced in August 2017. Primary outcomes at 12 months will be available for analysis from September 2019.

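### The primary endpoint set is defined in three inconsistent ways and every result is judged at P<.05, so the family-wise error rate is 5% only if EDNP at one time point is the sole primary

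*Protocol article*

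**What the plan says.** Three parts of the protocol article define the primary endpoint, and they differ.

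- **Abstract, Methods:** "Primary outcome measures at 6 and 12 months are changes in body mass, EDNP food and beverage consumption, and daily moderate-to-vigorous PA". That is three outcomes at two time points.
- **Statistical Analysis:** "The following primary outcome variables will be measured at baseline and 12 months of the intervention", followed by the same three outcomes. That is three outcomes at one time point. The Results section agrees on timing: "Primary outcomes at 12 months will be available for analysis from September 2019".
- **Power:** the trial is sized to "detect a change in the primary outcome variable of at least 0.6 median serves/day of EDNP (discretionary) foods", "at 90% power and 5% level of significance". The wording is singular, and neither body mass nor MVPA enters the calculation.

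The decision rule in Statistical Analysis is one flat threshold: P-"values < .05 will be considered statistically significant". It makes no distinction between outcomes or time points. The comparison is described as "Data on change in outcome variables in each of the two groups will be compared using analysis of covariance", although three groups are randomized.

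**The concern.** The three definitions give six, three or one primary test for a single group contrast. They also answer different questions. With a 6-month intervention and 6 months of follow-up, the 6-month result measures the effect at the end of the intervention and the 12-month result measures whether it lasts.

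Read literally, the text lets any of three to six results at P<.05 be presented as a primary success. The chance of at least one such result when nothing works is then above 5%. A reader of the final report could not tell from this article whether a significant 6-month MVPA result, for example, with null EDNP and body mass results, is a positive trial.

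**Working it through.** **Inputs from the document**

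- Per-test level .05 (Statistical Analysis). Sidedness is not stated; two-sided is assumed, in line with the 95% CIs.
- Primary outcomes: three at two times (abstract), three at one time (Statistical Analysis), one (Power).
- Target difference 0.6 EDNP serves/day, 90% power, 200 per group, 20% dropout (Power). No SD is given.
- One group contrast. Table 1 gives mobile food record and accelerometer data only for tailored feedback and active control, so one contrast is the natural reading for those two outcomes.

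**Step 1. The plan's own figures.** The 5% level reproduces for a single test: 1 − 0.95^1 = 0.05. The sample size can be neither confirmed nor refuted without an SD, but the implied SD can be back-solved:

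SD = 0.6 / [(1.960 + 1.282) × √(2/n)]

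- 200 analyzed per group: SD = 0.6 / (3.242 × 0.1000) = 1.85 serves/day
- 160 analyzed per group (200 less 20%): SD = 0.6 / (3.242 × 0.1118) = 1.66 serves/day

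**Step 2. Family-wise rate, independent tests.** The formula is 1 − 0.95^k.

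| Definition | k | Rate | Bonferroni upper bound |
|---|---|---|---|
| Power section (EDNP, one time point) | 1 | 5.0% | 5% |
| Statistical Analysis | 3 | 14.3% | 15% |
| Abstract | 6 | 26.5% | 30% |

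**Step 3. Family-wise rate, correlated tests.** Multivariate normal test statistics were simulated (500,000 draws, rejection at |z| > 1.96). The correlations are assumptions, not figures from the document: a common correlation between outcomes, and a correlation between the 6- and 12-month results of the same outcome.

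| Between outcomes | 3 tests | 6 tests, between times 0.3 | 6 tests, 0.5 | 6 tests, 0.8 |
|---|---|---|---|---|
| 0.1 | 14.2% | 25.8% | 24.8% | 21.5% |
| 0.3 | 13.6% | 24.8% | 23.7% | 20.6% |
| 0.5 | 12.5% | 23.1% | 22.0% | 19.1% |

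The ranges are roughly 12–14% for three tests and 19–26% for six.

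**Step 4. Power cost of controlling the rate.** At 90% power and .05 the standardized effect is 1.960 + 1.282 = 3.242, whichever n was the basis. The first Holm step for three outcomes is .05/3 = .0167, with critical value 2.394:

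Power = Φ(3.242 − 2.394) = Φ(0.848) = 80%

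If all six results stayed primary, the first step would be .05/6 = .0083, with critical value 2.638: Φ(0.604) = 73%.

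**The case against.** The case on the other side has real force.

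- **The document never claims 5% as a family-wise rate.** It sets a per-test threshold, and the 5% in Power belongs to the EDNP calculation. On the reading that EDNP at 12 months is the sole primary, for one contrast, the error rate is 5%. This stands. The inflation is conditional on the other two definitions and on any one success being enough. A rule requiring all three outcomes to succeed would also remove it, but none is stated.
- **14% and 26% are not the rate as such.** A reader might infer that the false-positive rate simply is 14% to 26%. Those values need independent tests, and 6- and 12-month changes in the same outcome are unlikely to be independent. This stands; they are values for the independent case.
- **Multiplicity procedures are commonly left to the SAP or full protocol**, which are not shown. So the absence of an adjustment method, or of sizing for body mass and MVPA, is not itself the point. What remains is what the article does state: three incompatible definitions and one flat threshold. A SAP method could not be applied without first choosing among them.
- **Most of the text points to 12 months.** Statistical Analysis and Results agree, and only the abstract sentence adds 6 months. A reader might infer that the investigators intend to choose the time point after seeing the data. Nothing in the document supports that; it shows only that the wording does not exclude it.
- **The phrase placing 12 months within the intervention** conflicts with the 6-month intervention period, but this is loose wording and has no bearing on error rates.
- **A power loss to 69% might be inferred** by testing at .0167 with 160 completers when 200 was the power basis. That mixes two effects: dropout alone takes 90% to about 83%, and only the remainder comes from the smaller alpha.

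**Conclusion.** The point holds as a contradiction in the primary endpoint definition, combined with a flat P<.05 rule. If any single significant primary result counts as success, the family-wise false-positive rate for one contrast is up to about 14% (Statistical Analysis) or 26% (abstract) under independence, and about 12–14% or 19–26% under the assumed correlations. It exceeds 5% in every multi-test scenario tried, and equals 5% only on the Power section's single-outcome reading at one time point. These figures assume two-sided tests and one contrast; further contrasts, for instance on self-reported body mass with the online control group, would raise them. The document does not support saying that the trial's error rate is 14% to 26% without those conditions, or that it promises 5% overall and breaks that promise. The definition should be settled before outcome data are examined, because it decides what counts as the trial's primary result.

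**What to change.** 1. State one primary definition and use it in the abstract, Statistical Analysis and Power. One option is the 12-month difference between tailored feedback and active control, with 6 months secondary; this fits Statistical Analysis and Results and needs only the abstract and Power wording aligned. Which time point is primary is for the investigators to decide, but it must be a single stated choice.
2. State how the three outcomes combine, by one of two routes:
   - **Fixed sequence**, with EDNP first because it is the only outcome sized, and the order of body mass and MVPA named in advance. Each is tested at .05 only if the one before it succeeds. This costs EDNP no power.
   - **Holm** across the three outcomes at a family-wise 5%, with power restated. EDNP power falls from 90% to about 80% at the first step (.0167). That is the worst case, since EDNP is tested at .025 or .05 if other outcomes reject first.
3. Give the SD behind the sample size, so that the restated power can be checked directly.

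The cost is wording, plus the lower stated power if Holm is chosen.

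### The only analysis that uses both follow-up visits together first makes continuous change binary, which costs precision in the longitudinal and predictor analyses but not in the ANCOVA

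*Protocol article*

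**What the plan says.** The Statistical Analysis section of the protocol article describes two analyses.

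- **Group comparison, continuous.** "Data on change in outcome variables in each of the two groups will be compared using analysis of covariance". The result stays on the outcome's own scale: "Effect size of differences between treatment and control will be expressed as adjusted mean difference and associated 95% CIs".
- **Follow-up visits, binary.** "Data on change in outcome variables postintervention and follow-up time points will be converted into binary categorical variables", and these are "analyzed using multivariable logistic regression and generalized estimating equations", reported as odds ratios.

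The purpose of the binary analyses appears in the closing sentence: "The analyses will identify characteristics of participants who are least likely to change their consumption of EDNP foods, PA, and BMI". The article says that the results will then serve to select groups for later programmes.

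On timing, the abstract says "Primary outcome measures at 6 and 12 months are changes in body mass", while the Statistical Analysis section opens with "The following primary outcome variables will be measured at baseline and 12 months of the intervention". The sentence on binary conversion is the only one in that section that brings the post-intervention and follow-up points together.

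**The concern.** Body mass, EDNP serves and MVPA minutes are continuous and are collected at baseline, 6 and 12 months (Data-Collection Procedures; Table 1). The trial has a 6-month intervention followed by 6 months of follow-up, so whether an effect lasts is part of the design. The one named method that could answer this from both visits, generalized estimating equations, is applied only after the size of each change has been thrown away. Someone just past the cut and someone far past it count the same, and the odds ratio depends on where the cut falls. The same model handles a continuous response equally well, so nothing is gained in exchange for the lost precision.

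The second issue is what the predictor results can support. A characteristic linked to little change need not be linked to little benefit from tailored feedback.

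**Working it through.** **Inputs**

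- Outcomes and visits: from the abstract, Data-Collection Procedures and Table 1.
- Cut-point, standard deviation and 6/12-month correlation: not stated. Assumed here: approximately normal change; a share p of participants counted as changed of 0.5, 0.3 or 0.2 (the results are the same for 1 − p); correlation ρ from 0.5 to 0.8.
- Completers: 200 per group less 20% drop-out (Power section) = 160.

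**The plan's own figure.** The article attaches no figure to the binary analysis. The 200 per group in the Power section cannot be reproduced because no standard deviation is given. Solving backwards for 0.6 serves/day at 90% power and two-sided 5%: SD = 0.6/(1.960 + 1.282) × √(160/2) = 1.66 serves/day with 160 completers, or 1.85 with 200. The loss calculation below does not depend on this.

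**Step 1: one visit.** The efficiency of a binary split of a normal outcome, relative to the continuous analysis, is E1 = φ(z_p)² / [p(1 − p)].

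| Split | E1 | Loss |
|---|---|---|
| 50/50 | 0.3989²/0.25 = 0.637 | 36% |
| 30/70 | 0.3477²/0.21 = 0.576 | 42% |
| 20/80 | 0.2800²/0.16 = 0.490 | 51% |

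**Step 2: average over two visits.** The variance of a two-visit mean is proportional to (1 + ρ)/2. Splitting lowers the between-visit correlation from ρ to a smaller binary correlation r, obtained from the bivariate normal, so the second visit recovers part of the loss: E2 = E1 × (1 + ρ)/(1 + r).

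| Split | ρ = 0.5 | ρ = 0.8 | Loss |
|---|---|---|---|
| 50/50 | 0.637 × 1.5/1.333 = 0.717 | 0.637 × 1.8/1.590 = 0.721 | about 28% |
| 30/70 | 0.576 × 1.5/1.318 = 0.656 | 0.576 × 1.8/1.577 = 0.657 | about 34% |
| 20/80 | 0.490 × 1.5/1.295 = 0.568 | 0.490 × 1.8/1.556 = 0.567 | about 43% |

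Within this range the correlation hardly matters.

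**Step 3: check on the approximation.** E1 is a large-sample result for small effects. At a standardised difference of (1.960 + 1.282)/√80 = 0.362, where 160 per group give 90% power on the continuous scale, the two-proportion calculation needs 253, 280 and 331 per group for the three splits. The ratios 160/253 = 0.632, 160/280 = 0.571 and 160/331 = 0.483 agree with E1 to within 0.01.

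**Step 4: outside the range.** A 10/90 split would lose 66% at one visit and about 59% over two.

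**Step 5: the predictor sentence.** Observed change in the tailored feedback group is the change that would have occurred anyway plus the effect of feedback. Without an arm-by-characteristic term, the coefficient of a characteristic reflects both parts. It answers who changed least. It does not answer in whom feedback worked least.

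**The case against.** The strongest reply is that the treatment comparison is never made binary. It is done by analysis of covariance, and the binary models serve a descriptive aim. That is correct, and it limits the point. A reader might infer that the trial's 90% power is at risk. Applying Step 1 to a two-group test with 160 per group, power = Φ(3.242 × √E1 − 1.960), gives about 73%, 69% and 62%. Those values would describe a binary test of treatment, and the article assigns that comparison to the continuous analysis, so they do not apply to it.

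Three other stronger readings are also unsupported.

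- That the analysis of covariance discards people who miss a visit: the article does not describe missing-data handling, which a full protocol or SAP may do.
- That the cut-point will be picked from the data: its absence from an article does not show this.
- That the predictor analysis is invalid without interactions: describing who changes least needs none, and the article neither excludes such terms nor says that these people respond less to feedback. It also lists the baseline value as a possible covariate, which bears on regression to the mean.

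Two further objections have weight. Normality is uncertain, since the Power section speaks of medians and the Statistical Analysis section allows for transformation; with heavy-tailed change the loss could be smaller. And with complete 12-month data, a repeated-measures model would add little to the 12-month contrast itself.

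What remains is a choice that the article states: continuous outcomes are made binary before the only joint use of the two follow-up points.

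**Conclusion.** The point holds in a limited form. The article's only named joint analysis of the two follow-up points gives up information that its own data contain: about 36% to 51% at one visit, or about 28% to 43% for a two-visit average. These ranges rest on approximate normality, a 20% to 80% share counted as changed and, for the second range, a 6/12-month correlation of 0.5 to 0.8. None of these is given in the article. The loss affects the longitudinal and predictor analyses, and the main between-group estimate stands. The predictor limb survives only as a limit on interpretation: the results should not be read as showing who responds to tailored feedback. The change is worth making because it improves a stated method at almost no cost.

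**What to change.** Replace the binary longitudinal analysis with one continuous repeated-measures model per outcome: a linear mixed model, or identity-link generalized estimating equations with robust standard errors. Use the 6- and 12-month values as responses, with arm by time, baseline value and sex (both randomization stages are run separately by sex). Include all participants with any follow-up in the arms where that outcome is measured, and report the adjusted mean difference at each time.

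Keep binary responder results only as a supplement, with cut-points fixed in advance.

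Model predictors of change on the continuous scale too. If they are to say who responds to tailored feedback, base that on arm-by-characteristic interactions labelled exploratory; otherwise describe them only as predictors of change.

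The cost is revised wording and slightly more programming, with no new data. The drawback is that the interaction tests will have low power.
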